### Strategies to improve adherence to interventions {11c}

The adherence reminder sessions will take place 15 min before every training session. This session will include the following:
The importance of following a training program for general health.Instructions about how to practice carefully and how to avoid physical collision between participants, especially in competitions or games.The importance of adherence in order to develop the performance of the body, and the negative effects of absence from any training session.Instructions about the purpose of the study and the training plan.Instructions the importance of informing the coach about any injury or physical pain.Participants will have an opportunity to ask questions throughout the training program at any time.

Before the starting of every single month of the training program, there will be a special recreational trip in order to increase the motivation and commitment of participants.

### Relevant concomitant care permitted or prohibited during the trial {11d}

Participants are allowed to take an additional break in the first training sessions.Participants should not eat a meal at least 2 h before the exercise.Participants should not use any additional assistive equipment during exercise.

### Provisions for post-trial care {30}

Although health insurance is free of charge in Syria, the first author will be responsible for any injury that occurs during the training sessions, and he will sign a paper for each participant proving his commitment to providing any medical treatment throughout and after the intervention period in coordination with Tishreen University Hospital.

### Outcomes {12}

#### Primary outcome: muscle architecture, tendon length, tendon thickness, muscle power, torque, and work

Muscle CSA, FL, MT, and PA will be examined with ultrasound imaging (Esaote, Technos MPX) in B-mode with a 10-MHz linear array transducer. This technique uses sound waves at fixed frequencies to create real-time images of the limb musculature in vivo (Esaote, Technos MPX, ultrasound). Conventional B-mode ultrasound can provide both quantitative and qualitative information on skeletal muscle tendons and ligaments [50]. Muscle ultrasound is a reliable method for the measurement of human FL, PA [33], and MT in B-mode images [46]. Also, ultrasound is a reliable and valid tool for the assessment of muscle size in older adults, ICC scores ranging from 0.92 to 0.999 [11].

Each of muscle power, torque, and work will be measured using isokinetic dynamometer test. An isokinetic dynamometer (Genu3 Easytech, Florence, Italy) will be used to estimate knee range of motion (ROM), passive resistive torque, power, and work for thigh muscles in an angular speed of 90° per second. Test-retest reliability will take place 2 weeks before the intervention (the same test twice over a period of time to a group of individuals). The scores from time 1 and time 2 can then be correlated in order to evaluate the test for stability over time. The Pearson product-moment correlation coefficient will be used to measure the strength of the linear relationship between the variables. Three to four submaximal practice trials will be given before each of the assessments. Knee extensor and flexor muscle power and work will be measured as the peak torque obtained over 3 trials during an isokinetic contraction using the passive concentric mode to test throughout the entire range of motion. Passive resistive torque will be obtained over 3 repetitions at the same speed degree. Peak torque will be gravity corrected using the Genu3 Easytech software.

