#### Secondary outcomes: explosive power, aerobic capacity, and tendon CSA and length

The explosive power will be measured by using vertical jump test. The test is often used as a measurement of lower-body power [44] and thus as an indirect measure of performance. Vertical jump testing has been shown to be a valid and reliable measure of lower-body explosive power [44].

The high-intensity aerobic capacity will be measured by the YYIR tests. The test is a simple method for examining an athlete’s capacity to perform a repetitive high-intensity aerobic exercise [9]. Yo-Yo test has been repeatedly proven as reliable (ICC = 0.86 to 0.95) [49], and also, YYIR1 has been proven as a valid and reliable tool with high reproducibility for measuring high-intensity aerobic capacity from various sports and competition levels [16, 27], and a moderately reliable predictor of VO2 max [44, 49].

Tendon CSA and length will be measured using ultrasound imaging (Esaote, Technos MPX) in B-mode with a 10-MHz linear array transducer the same as muscle architecture measurements.

The muscle architecture and PT length measurements will take place from 1 March 2020 until 10 March 2020 for both groups in Tishreen University Hospital (Radiology Department). After that, the measurements of torque, power, and work will take place until 16 March 2020 in Tishreen University Hospital (Physical Therapy Department). Explosive power and aerobic capacity measurements will start directly after that until 20 March 2020 at Latakia Sports City Stadium.

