### Sample size {14}

The sample size was calculated by using “Gpower” software 3.1.9.2. For the determination of the effect size, we made a pilot study which included 10 participants from every single group. We measured the PA of VM for both groups. The mean (M) for football group was 10.59 and 8.17 for AG. Also, the standard deviation (SD) for FG was 2.80 and 2.01 for aerobic one. Based on this, the effect size was 0.992. The α level was 0.05, and the power was 0.95. The minimum numbers of sample were 46 participants.

We raise the sample to 60 for better result. Sixty untrained but healthy adult men are equally divided into two groups (mean ± SD age 55 ± 5). This sample includes a dropout of 15% and provides a moderately detectable change between a group with an alpha level of *p* < 0.05. Some of them had experienced some of the age-related neuromuscular problems or diseases, at least within the last year.

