## Data collection and management

### Plans for assessment and collection of outcomes {18a}

#### Ultrasonography

Participants will report to the Human Performance Laboratory for ultrasound measurements after 72 h without any vigorous physical activity. They will be instructed to lay supine for 15 min to allow fluid shifts to occur before image collection. A 10-MHz linear probe scanning head (LA523 13-4) will be used to optimize spatial resolution and coat with water-soluble transmission gel and positioned on the skin surface to provide acoustic contact without depressing the dermal layer to collect the image. The length of the muscle fascicles and the PA, which is the angle of insertion of the fascicles into the muscle’s aponeurosis, represent the main structural parameters that can be detected via the conventional B-mode ultrasound modality [41]. Measures of CSA and FL will be obtained using a sweep of the muscle in the extended field of view mode with the gain set to 50 dB and image depth to 5 cm. The FL of rectus femoris (RF) and VM will be measured using “the intercept method” with this formula: FL = visible FL + predicted length [13].

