All measures will be in the RF, vastus lateralis (VL), VM, and PT of the dominant leg. Subsequent measures will be taken using the same limb positioning and anatomical site and will be performed by the same examiner. After scanning, all images will be analyzed with image analysis software (ImageJ, version 1.45s), which quantifies muscle quality in the form of echo intensity (EI). A known distance of 1 cm as shown in the image will be used to calibrate the software program [13]. For the measures of RF and VM, the participant will be placed supine on an examination table, according to the American Institute of Ultrasound in Medicine, with the legs extended but relaxed and with a rolled towel beneath the popliteal fossa allowing for a 10 bend in the knee as measured by a goniometer. For measures of the VL and VM, participants will be placed on their non-dominant leg side with the legs together and relax to allow a 10 bend in the knee as measured by a goniometer. The measurement of RF CSA will be taken in the sagittal plane parallel to the long axis of the femur, and scanning occurs in the axial plane perpendicular to the tissue interface at 50% of the thigh length. Fifty percent of thigh length is determined as halfway from the anteroinferior iliac spine to the proximal border of the patella. VL and VM CSA measure at 50% of the distance from the most prominent point of the greater trochanter to the insertion. For all muscles, consecutive CSA images will be analyzed using the polygon tracking tool in the ImageJ software to obtain as much lean muscle as possible without any surrounding bone or fascia.

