However, so far, almost no studies compared the effects of football and running training interventions on the age-related decline of muscle strength and structure. This is the first study that aims at investigating the differential effects of football and running training response on muscle architecture, patella tendon properties, and thigh muscles. The proposed study should benefit participants’ physical, psychological, and social dimensions. It is assumed that running and football training not only may result in the improvement of the aerobic capacity and systemic arterial blood pressure reductions, but also can improve the functional parameters, including increased explosive power strength, balance, agility, and functional capacity. As our primary hypothesis, we expect moderate differences between both groups in muscle architecture CSA, FL, MT, PA, knee ROM, passive resistive torque, work, power, and tendon length and thickness as football entails are broader and multimodal muscular stimulus compared to aerobic training alone. These may lead to overall decrease in obesity risk and stress, and it could also prevent heart diseases, maintain muscle mass, and reduce the risk of depression. Moreover, the training programs may enhance muscle architecture and tendon thickness that causes a perceptible decrease in the probability of dynapenia and sarcopenia in the future.

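### The primary outcome is an unranked set of about 17 to 23 variables whose membership changes between sections, with tendon length both primary and secondary, while the trial is sized on one variable

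*Protocol article*

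**What the plan says.** All references are to the protocol article.

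- **Outcomes {12}, primary.** The heading is "Primary outcome: muscle architecture, tendon length, tendon thickness, muscle power, torque, and work". The text beneath it adds that "Muscle CSA, FL, MT, and PA will be examined with ultrasound imaging" and that "Knee extensor and flexor muscle power and work will be measured as the peak torque obtained over 3 trials". It also names knee range of motion (ROM) and passive resistive torque among the dynamometer measures.
- **Outcomes {12}, secondary.** The heading is "Secondary outcomes: explosive power, aerobic capacity, and tendon CSA and length", so tendon length appears a second time.
- **Ultrasonography, under {18a}.** "All measures will be in the RF, vastus lateralis (VL), VM, and PT of the dominant leg". The sentence on the fascicle-length formula names only two muscles: "The FL of rectus femoris (RF) and VM will be measured using" the intercept method.
- **Objectives {7}.** The main objective lists muscle thickness, muscle length, fascicle length, pennation angle, patellar tendon length, power, work and torque. It has neither cross-sectional area (CSA) nor tendon thickness.
- **Discussion.** "As our primary hypothesis, we expect moderate differences between both groups in muscle architecture CSA, FL, MT, PA". The sentence goes on to knee ROM, passive resistive torque, work, power, and tendon length and thickness.
- **Sample size {14}.** "We measured the PA of VM for both groups". Alpha is 0.05, power 0.95, effect size 0.992, minimum total 46, raised to 60 with 15% dropout included.
- **Statistical methods {20a}.** Paired and independent-samples t tests are planned. No outcome is placed ahead of another, and no adjustment is mentioned.

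**The concern.** A reader cannot tell which result will count as the trial's answer. Every variable in the primary set has the same standing, the set itself is not stable, and one of its members is also secondary. Whichever variable shows a difference could be presented as the primary finding.

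The sample size gives a type I error and power for one variable only, and nothing in the outcomes section singles that variable out. A later analysis plan could add a multiplicity rule, but such a rule needs a defined family to act on, and this document gives several.

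**Working it through.** **1. The lists side by side**

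| Variable | Objectives | Primary outcome section | Secondary heading | Primary hypothesis |
|---|---|---|---|---|
| Muscle CSA | no | yes | no | yes |
| Muscle length | yes | no | no | no |
| Tendon length | yes | yes | **yes** | yes |
| Tendon thickness | no | yes | no | yes |
| Knee ROM | no | in text, not in heading | no | yes |

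Table 4 schedules ROM, power, work, muscle architecture and tendon length, but neither torque nor tendon thickness.

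**2. Count of primary variables**

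- Architecture: 4 parameters × 3 muscles = 12.
- Tendon length and tendon thickness: 2.
- Power and work, extensor and flexor: 2 × 2 = 4.
- Passive resistive torque and ROM: 2.
- Total: 12 + 2 + 4 + 2 = 20.

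Lower reading: drop vastus lateralis fascicle length, ROM and tendon length, 20 − 3 = 17. Higher reading: add extensor and flexor peak torque, and muscle length once, 20 + 3 = 23.

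**3. The plan's own figure**

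- d = (10.59 − 8.17) / √((2.80² + 2.01²)/2) = 2.42 / 2.437 = 0.993; the plan states 0.992.
- The noncentral t distribution with d = 0.992, alpha 0.05 and power 0.95 gives N = 46 for a **one-sided** test (power 0.952), which matches the plan. A two-sided test needs N = 56, and 46 participants give two-sided power 0.908.

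**4. Familywise error for k tests at 0.05, no true difference**

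- Independent: 1 − 0.95^k. For k = 17, 20 and 23 this is 58.2%, 64.2% and 69.3%.
- Equal correlation ρ between two-sided z tests: 1 − E[{Φ((1.96 − √ρ·Z)/√(1−ρ)) − Φ((−1.96 − √ρ·Z)/√(1−ρ))}^k], with Z standard normal. The documents give no correlations, so ρ is an assumption:

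| ρ | k = 20 | k = 6 (one test per named domain) |
|---|---|---|
| 0 | 64% | 26% |
| 0.3 | 54% | 24% |
| 0.5 | 42% | 21% |
| 0.7 | 29% | 16% |
| 0.9 | 16% | 11% |

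The expected number of false positives among 20 tests is 20 × 0.05 = 1, whatever the correlation.

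**5. Power under the two remedies, d = 0.992, two-sided**

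Noncentrality = d·√(n₁n₂/(n₁+n₂)). Completers after 15% dropout: 60 × 0.85 = 51.

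- One primary at 0.05: with 26 + 25, noncentrality 0.992 × √(650/51) = 3.54, power 0.935. With 30 + 30, noncentrality 0.992 × √15 = 3.84, power 0.965.
- Bonferroni over 20 (0.05/20 = 0.0025): power 0.75 with 30 per arm and 0.62 with 25 per arm. N = 94 would be needed for 95% power.

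**The case against.** The best case against the point has four parts.

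- **The plan does not say that each variable is tested at 0.05 without correction.** This stands. The only alpha is in the sample-size section, and multiplicity rules are often left to an analysis plan that is not shown. The absent correction is therefore not the finding. What this document does fix, and fixes badly, is an unranked primary list whose members differ between sections.
- **A reader might infer that a chance primary difference is more likely than not.** The documents do not support that. For 20 tests it needs independence or weak correlation; at 0.5 the figure is already 42%. The ultrasound outcomes all come from one leg, often from one muscle, so independence is the least plausible case. What holds is that the error rate stays well above 5% over the whole range shown.
- **The count is a matter of reading.** This also stands. The text describes power and work as peak torque, so they may not be separate quantities, and the fascicle-length formula omits vastus lateralis. Even one test per named domain gives 26% if independent and 11% at a correlation of 0.9.
- **Naming a primary now may be a post hoc change.** Training was due to end on 15 July 2020 and the article is dated 9 December 2020. This is a fair warning and shapes the fix.

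**Conclusion.** The point holds. Tendon length in both lists and the differing primary sets can be read directly from the text and need no calculation. The inflation figures rest on three assumptions: about 20 tests, each at 0.05, and a common correlation that the documents do not give. On those terms the chance of at least one false-positive primary result is 16% to 64%, about three times nominal or more.

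A reader might also infer that the stated 0.05 and 0.95 are secure at least for VM pennation angle. That goes too far: 46 participants reach 0.95 only one-sided, and 51 completers give about 0.93 two-sided. The shortfall is small and does not weaken the case for making this variable the primary.

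This should be corrected, because as written the plan does not determine which result is confirmatory.

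**What to change.** 1. Before any between-arm results are seen, name the between-arm difference in VM pennation angle as the single primary outcome, since it is the only variable the trial was sized on. State the time point, because the sample-size section does not say whether the pilot values were taken before or after training. Disclose the change and its date. If between-arm results have already been seen, say so in the report and do not present any one variable as the pre-specified primary.
2. Report the other variables as secondary with Holm adjustment, or as exploratory estimates with 95% confidence intervals.
3. List tendon length once. The Objectives and the Discussion treat it as primary and the secondary heading does not, so the sections must be reconciled; under a single primary it falls with the remaining variables. Align the Objectives, both outcome headings, Table 4 and the primary hypothesis.
4. State that two-sided power for this primary at d = 0.992 is about 0.93 with 51 completers and 0.965 if all 60 complete.

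The cost is wording in the protocol and registry, with no added participants. The downside is that the other architecture, tendon and dynamometer variables lose the primary label. Keeping all 20 as primary under Bonferroni would cost far more, with power of 0.75 at 30 per arm.

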#### PA

The PA of the rectus femoris, vastuss lateralis, and vastus medialis will be measured using B-mode ultrasound at the same site as MT and CSA [1]. The transducer will be longitudinal to the muscle tissue interface, and 1 image will be analyzed offline. Muscle fiber will be determined as the intersection of the fascicles with the deep aponeurosis.

PT length will be measured via ultrasound scans (Esaote, Technos MPX, ultrasound) at knee joint angle of 90° (0° corresponding to full extension), as the distance between tendon insertions on the patella apex and the tibial tuberosity. Tendon CSA will be measured from transversal ultrasound scans (linear array transducer 5 cm, LA523, 10 MHz transducer). The reliability of this technique has been shown previously [45]. PT CSA is obtained as the average of two measurements performed at the proximal (CSAp) and distal (CSAd) insertions and at tendon mid-length (CSAm). The mean CSA of these three scans’ positions will be used for further analysis. PT length will be measured as the distance between the proximal insertion of the PT and the tibial insertion. The use of ultrasound to perform quantitative measurements of musculoskeletal tissues has shown reliability (tendon CSA: ICC of 0.91–0.98 and 0.96–0.98 for tendon length) [20].

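### Pearson's r is the only statistic planned for dynamometer test-retest stability, and it cannot detect a systematic shift between the two tests

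*Protocol article*

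**What the plan says.** The plan for the reliability check stands in the primary outcome part of Outcomes {12}, in the paragraph on the isokinetic dynamometer. That device "will be used to estimate knee range of motion (ROM), passive resistive torque, power, and work for thigh muscles". Power, torque and work belong to the primary tier, under the heading "Primary outcome: muscle architecture, tendon length, tendon thickness, muscle power, torque, and work".

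The check is a repeat of the same test: "Test-retest reliability will take place 2 weeks before the intervention". Its aim and method are given together: "The scores from time 1 and time 2 can then be correlated in order to evaluate the test for stability over time". The coefficient is then fixed: "The Pearson product-moment correlation coefficient will be used to measure the strength of the linear relationship between the variables".

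No agreement statistic is planned beside it. Neither this paragraph nor Statistical methods {20a} mentions an ICC for the trial's own data, a mean difference between the two tests, limits of agreement or a standard error of measurement. No acceptance threshold for r is stated. For other instruments the article cites ICCs from the literature, for example "tendon CSA: ICC of 0.91–0.98 and 0.96–0.98 for tendon length" for the patellar tendon.

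Statistical methods {20a} plans two families of t tests: paired tests within each group, to measure what each programme achieves, and independent-samples tests between the football and aerobic groups.

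**The concern.** The article does not leave the choice of reliability statistic to a later document. It names one coefficient and states what that coefficient is to establish, and the two do not match. A test is stable over time, in the absolute sense, if the same man obtains about the same score on both occasions. A correlation addresses something narrower: whether men who score high the first time also score high the second time.

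The difference matters for a maximal-effort task on an unfamiliar machine in untrained men. The plausible failure there is that most of them do somewhat better the second time because they have learned the task. That is a systematic shift, and r does not register it.

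Two things are at stake. The first is the reliability conclusion itself, since a high r could accompany a material drift. The second is the interpretation of the paired before-after changes in torque, power and work. Both arms train, so no untrained group separates practice from training. The trial's own test-retest step is a place where the practice component could be measured, and the planned statistic discards that information.

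**Working it through.** There is no stated reliability figure to reproduce. The protocol gives no expected r, no expected shift and no number of men for the retest. The check is therefore algebraic, and r and the shift below are assumptions.

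**1. Pearson's r ignores shift and scale.** For test scores X and retest scores Y, and constants b > 0 and c, corr(X, bY + c) = corr(X, Y). A uniform gain c or a rescaling b leaves r unchanged.

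**2. Absolute agreement does not ignore a shift.** Take equal variances of 1 on each occasion, correlation r, and a mean shift of k SD. The variance components are:
- between men: r
- residual: 1 − r
- between the two occasions: (k/2)² + (k/2)² = k²/2

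The single-measure absolute-agreement ICC is the between-men component divided by the total:

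ICC(A,1) = r / [r + (1 − r) + k²/2] = r / (1 + k²/2)

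The divisors are 1.03125 for k = 0.25, 1.125 for k = 0.5 and 1.5 for k = 1.0.

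| Assumed r | No shift | 0.25 SD | 0.5 SD | 1.0 SD |
|---|---|---|---|---|
| 0.80 | 0.80 | 0.78 | 0.71 | 0.53 |
| 0.90 | 0.90 | 0.87 | 0.80 | 0.60 |
| 0.95 | 0.95 | 0.92 | 0.84 | 0.63 |

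For example, 0.90/1.125 = 0.80 and 0.95/1.5 = 0.63. Pearson's r equals the first column throughout its row.

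**3. Check by simulation.** With 200,000 simulated pairs at r = 0.90 and shifts of 0, 0.5 and 1.0 SD, Pearson's r was 0.900 each time. ICC(A,1) was 0.900, 0.799 and 0.599. Multiplying the retest scores by 1.2 also left r at 0.900.

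**4. The form of ICC matters.** In the same simulation the consistency ICC stayed at 0.900 under every shift. Asking for an ICC without naming the form would not cure the problem.

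**5. Where a shift enters the planned tests.** Let a practice gain c be common to both arms.
- Between arms after training: (mean FG + c) − (mean AG + c) = mean FG − mean AG, so c cancels.
- Within an arm: (post mean + c) − pre mean = true change + c, so c is counted as change.

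**The case against.** The strongest reply is that nothing in the trial depends on r. No threshold is set, the sample size comes from a pilot of vastus medialis pennation angle, and {20a} does not use the reliability result. Every paired t test and its p-value would be the same whichever coefficient was reported. The exposure of within-arm changes to practice arises from having no untrained arm. This stands: a better coefficient does not remove a practice effect, but only makes it visible when the changes are read.

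Four further limits stand:
- Rank-order stability is a real part of reliability, and r measures it.
- Practice is planned before testing, both in the primary outcome section and in the isokinetic power and work section under {18a}. That may reduce a learning shift, though it does not measure one.
- Small shifts cost little: at 0.25 SD, agreement falls only from 0.95 to 0.92 or from 0.90 to 0.87.
- The ICCs cited for other instruments are given without their form, so they may be blind to a shift too. The contrast with them proves little.

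Three stronger readings are tempting. A reader might infer that the comparison of football with aerobic training is biased. It is not biased by a shift common to both arms, and the documents give no reason to expect different practice effects. A reader might extend the point to the ultrasound outcomes, but the reliability plan sits with the dynamometer measures. Finally, a reader might infer that the retest comes too late. Two weeks before the 15 April start is about 1 April, whereas "the measurements of torque, power, and work will take place until 16 March 2020". The text does not say who is retested or exclude the March test as the first of the two occasions. A reliability estimate can also describe measurement error without preceding baseline. The dates need reconciling, but they do not show a flaw in the analysis.

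**Conclusion.** The point holds in a limited form. For the dynamometer measures (range of motion, passive resistive torque, power and work), the only planned statistic captures relative position and is blind to a systematic shift or change of scale. It cannot establish the absolute stability it is meant to assess.

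The mathematical statement needs no assumption about the data. The size does: the tabulated values assume equal variances on the two occasions, and r and the shift are illustrative. On those terms the gap between r and absolute agreement runs from about 0.03 at a shift of 0.25 SD to about 0.3 at 1.0 SD.

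The consequence is modest. It touches the reliability conclusion and the interpretation of within-arm changes in measures that include named primary outcomes. It does not touch the between-group comparison, which is the trial's main question.

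**What to change.** In the dynamometer paragraph of the primary outcome section, replace Pearson's r with a two-way, absolute-agreement ICC with 95% CI, naming that form explicitly. From the same two tests, also report the mean test-retest difference and the standard error of measurement. The mean difference is needed because a standard error taken from the residual variance does not contain the shift. Add a line to {20a} saying that within-arm changes in these measures will be read against the mean difference and the standard error of measurement.

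Separately, state how the reliability tests two weeks before training relate to baseline dynamometry ending on 16 March, and who is retested.

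The cost is a few sentences of text and a standard SPSS procedure, with no extra participants or tests.
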